### Control group

Participants randomized into the control condition will be instructed to complete the same online surveys (baseline, 2-,4-, and 8-week surveys) sent via email. Control participants will be given the option to access the intervention upon completion of their final assessment at 8-weeks. Along with participants in the experimental group, they will also receive a list of national and local resources for information about the effects of vaping in young people and help with reducing vaping behaviors after completion of the final assessment.

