**Methods:**

A 2-arm pilot randomized controlled trial (RCT) will be conducted by recruiting young adults ages 18–24 who reported vaping at least once per week in the past 30 days and having never smoked cigarettes at baseline. Participants will be recruited via social media ads and be randomly assigned to an intervention arm, which will be the Live Free From E-cigarettes (LIFFE) mobile-based program (*n* = 50), or a waitlist control arm (*n* = 50). The primary outcomes are biochemically verified 7-day point prevalence abstinence for nicotine vaping, vaping reduction, and smoking susceptibility. Outcomes are measured at 2-, 4-, and 8-weeks after randomization.

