### Study procedure

After signing the consent form, participants will complete a 20-minute baseline survey. Upon completion of the baseline survey, all participants will receive a $25 gift card and be randomized to the intervention (*n* = 50) or the waitlist control condition (*n* = 50). We will utilize stratified randomization to ensure that an equal number of males and females are randomized into each condition. Those randomized into the intervention will be prompted by research personnel to complete the 30-minute intervention, which will be delivered via a webpage accessible through a mobile device. More specifically, participants will be emailed a web link to access the intervention along with personalized log-in information consisting of their email address and a unique 4-digit PIN code. We will collect backend data indicating whether participants have completed all intervention components. We anticipate that most or all participants will complete the intervention given the 100% completion rate in one sitting among those who beta tested our program (completed June 2024; *N* = 20). However, if there are participants who have not completed the full intervention within 24 h of being given access to the program, research personnel will send a text and email reminder. All participants will then complete brief surveys, which will include the same measures from the baseline survey, 2, 4-, and 8-weeks post-randomization (see Fig. 1), to determine the efficacy of the program on reducing vaping and susceptibility to smoking in the immediate term (2-weeks post-randomization) and short term (4- and 8-weeks post-randomization). At most, three text messages and three emails will be sent to remind participants to complete the assessments. Those who do not respond despite the reminder attempts are counted as dropout at each time point. However, participants who do not respond in the previous assessment waves will still be contacted for later assessments. For instance, a participant who did not complete the 2-week follow-up assessment will still be asked to complete the 4-week assessment. Participants will receive a $25 Amazon gift card for completing each survey (up to $100 total). Participants will also be offered raffle tickets for a chance to win various prizes (e.g., movie tickets, $50 Amazon gift card). More specifically, participants will receive one raffle ticket for each survey they complete within two days of receiving the survey via email, giving them the opportunity to earn up to four raffle tickets. Participants who complete all four surveys within two days of receiving them will earn an additional three raffle tickets.

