#### Primary outcomes

Our primary outcomes are reductions in past 7-day self-reported vaping frequency (i.e., the number of days they vaped, the number of times per day they picked up their device to vape, and the number of puffs taken before putting their device away per day in the past 7 days), biochemically verified 7-day point prevalence abstinence, and smoking susceptibility using the 4-item Expanded Susceptibility to Smoking Index [35]. At each follow-up assessment, participants who report 7-day abstinence will be mailed a saliva cotinine test kit to provide biochemical verification of their abstinence. Participants will be provided with written instruction on how to perform the saliva cotinine test but will also be contacted by a research team member via a Zoom video call during verification to ensure that participants are able to correctly complete the test. Results will be provided immediately via the test strip and shown to the research team member to verify. Those with a cotinine level of < 30 ng/ml will be reported as having achieved biochemically verified nicotine vaping abstinence. Participants who complete this cotinine test will be compensated with a $20 Amazon gift card.

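### Controls may open LIFFE after the 8-week survey but before the mailed cotinine test that decides their week-8 verified abstinence

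*Protocol article*

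**What the plan says.** Four parts of the protocol article bear on this point.

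- **Release of LIFFE to controls (Control group):** "Control participants will be given the option to access the intervention upon completion of their final assessment at 8-weeks". The same section lists online surveys as the controls' tasks. It also gives a list of help resources to both arms once the final assessment is complete.
- **What an assessment is (Study procedure):** follow-up is described as "All participants will then complete brief surveys, which will include the same measures from the baseline survey". Shortly afterwards the article says that "three text messages and three emails will be sent to remind participants to complete the assessments". The second phrase refers to the same surveys.
- **How abstinence is verified (Primary outcomes):** "At each follow-up assessment, participants who report 7-day abstinence will be mailed a saliva cotinine test kit to provide biochemical verification of their abstinence". The test takes place on a video call: "Results will be provided immediately via the test strip and shown to the research team member to verify". The result settles the endpoint: "Those with a cotinine level of < 30 ng/ml will be reported as having achieved biochemically verified nicotine vaping abstinence".
- **Status and timing (Abstract, Methods):** verified 7-day abstinence is one of the primary outcomes, and "Outcomes are measured at 2-, 4-, and 8-weeks after randomization". The Primary analysis section compares it between arms by logistic regression.

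**The concern.** The control condition should last until the last control outcome has been measured. As written, it can end when the survey is submitted, while one primary outcome still waits for a kit in the post. In that interval a control who has just reported abstinence may take up LIFFE, which teaches quitting strategies. The participant is then tested and counted as an untreated control. The intervention arm has the same postal delay but no new access to LIFFE during it, so the arms are not treated alike.

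At stake is the last of the three between-arm abstinence comparisons. If LIFFE helps some of these controls to pass, the control rate rises and the difference shrinks. The Limitations section also plans to report whether effects wane over the 8 weeks. A control rate raised at week 8 only, with weeks 2 and 4 untouched, could be mistaken for waning.

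**Working it through.** The article gives no figure for this point: no expected abstinence rate, no uptake of LIFFE among controls and no interval from survey to test. Its power analysis is in terms of effect size f and does not address abstinence. The main check is therefore the order of events.

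**Order of events for a control at week 8**

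1. The control completes the 8-week survey and reports 7-day abstinence (Study procedure; Primary outcomes).
2. Completing the final assessment opens optional access to LIFFE (Control group). Study procedure and Control group both describe the assessments as surveys, so the trigger falls at step 1.
3. A kit is posted because of the answer given at step 1 (Primary outcomes), so the test comes later by at least the mailing time.
4. The strip is read on a video call and the 30 ng/ml cut-off decides the outcome.

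LIFFE takes 30 minutes (Development of the intervention), and beta testers averaged 24.29 minutes (Intervention engagement). It can easily be finished between steps 2 and 4. No section makes step 2 wait for step 4 or sets a limit on the interval.

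**What is and is not exposed**

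| Measure | Collected before control access? |
|---|---|
| All outcomes at weeks 2 and 4 | Yes |
| Week-8 vaping frequency | Yes (survey) |
| Week-8 smoking susceptibility | Yes (survey) |
| Week-8 self-reported abstinence | Yes (survey) |
| Week-8 cotinine result | Not necessarily |

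Only participants who report abstinence receive a kit, so the result can change only for controls who report abstinence and would otherwise fail the test.

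**Size**

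With 50 controls, one altered result moves the control rate by 1/50 = 2 percentage points.

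For a range, let s be the share of controls reporting abstinence at week 8. Let v0 be the share of those who would pass without early access, and v1 the share who pass when access is open. The verified control rate moves from s × v0 to s × v1, so

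shift = s × (v1 − v0), and at most s × (1 − v0).

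The term v1 − v0 already includes uptake: it is zero if nobody opens LIFFE before the test. All values below are assumptions.

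| s | v0 to v1 | Control rate | Shift (points) | Controls (of 50) |
|---|---|---|---|---|
| 10% | 80% to 90% | 8% to 9% | 1 | 0.5 |
| 10% | 60% to 80% | 6% to 8% | 2 | 1.0 |
| 10% | 50% to 100% | 5% to 10% | 5 | 2.5 |
| 20% | 80% to 90% | 16% to 18% | 2 | 1.0 |
| 20% | 60% to 80% | 12% to 16% | 4 | 2.0 |
| 20% | 50% to 100% | 10% to 20% | 10 | 5.0 |
| 30% | 80% to 90% | 24% to 27% | 3 | 1.5 |
| 30% | 60% to 80% | 18% to 24% | 6 | 3.0 |
| 30% | 50% to 100% | 15% to 30% | 15 | 7.5 |

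The rows ending at 100% are ceilings: every control who would otherwise fail would have to open LIFFE in the gap and pass because of it.

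To show what a middle row would mean, assume 30% verified abstinence in the intervention arm, 50 per arm and two-sided alpha 0.05. Power is Φ[(Δ − 1.96 × SE0)/SE1], with SE0 pooled and SE1 unpooled.

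- Control 12%: Δ = 0.18, SE0 = √(2 × 0.21 × 0.79/50) = 0.0815, SE1 = √((0.30 × 0.70 + 0.12 × 0.88)/50) = 0.0794; power 0.60.
- Control 16%: Δ = 0.14, SE0 = √(2 × 0.23 × 0.77/50) = 0.0842, SE1 = √((0.30 × 0.70 + 0.16 × 0.84)/50) = 0.0830; power 0.38.

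This shows sensitivity to a shift of two participants. It does not predict that such a shift will occur.

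**The case against.** The best defence is that the final assessment includes its verification. Primary outcomes speaks of posting the kit at each follow-up assessment, so an assessment might not count as complete until the strip has been read. On that reading the trigger already falls after the test. The reading is possible, but the article nowhere states it, and Study procedure uses the word for the surveys. Staff following the text literally would release LIFFE when the survey is submitted.

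A second defence is that the timing of log-in release is operational detail, which a journal article leaves to the full protocol. That would be a good answer if the article were silent. It is not: it states a release trigger, and as worded the trigger comes before a primary measurement is complete.

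A third defence concerns size, and it stands. The path needs a control who reports abstinence, would otherwise fail the test, opens LIFFE while the kit is in the post, and passes because of it. The likely bias is toward no effect, so it should not produce a spurious benefit. The trial is a 100-person pilot.

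A reader might also infer that the resource list adds to the bias. The documents do not support this: the list goes to both arms on the same trigger, so it creates no difference between them.

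**Conclusion.** The point holds in a limited form. Followed as written, the article lets a control who reports abstinence at week 8 take up LIFFE before the cotinine test that decides verified abstinence. This may raise the control rate and dilute the week-8 comparison. It rests on reading the final assessment as the survey, which is how the article mostly uses the word.

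Two stronger readings go too far. One is that week-8 abstinence in controls is measured after they cross over. Access is only an option, so the text supports *can be*, not *is*; a test after the trigger is not necessarily a test after exposure. The other is that the week-8 results as a whole are compromised. Only the cotinine component is exposed.

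The size is unknown and probably small. The one firm figure is 2 percentage points per altered result. The range of 1 to 15 points in the table rests wholly on assumed rates, and its upper end is a ceiling. The change is worth making because it costs almost nothing and protects a primary comparison.

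**What to change.** In the Control group section, state that control access to LIFFE opens after the 8-week survey and, for controls who report 7-day abstinence, only after the cotinine test has been completed or a fixed test window has closed. The window should be given as a number of days, so that a control who never takes the test is not kept waiting indefinitely. The resource list can follow the same later trigger in both arms; this is for consistency, since its present timing favours neither arm.

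The cost is one sentence and a short wait for the few controls who report abstinence. Sample size, outcome definitions and analysis do not change.

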### Measures

#### Screening variables

To screen for eligible participants and to characterize those who enroll into the study, we will gather information about demographics (age, gender, sex at birth, race, ethnicity, college attending status, U.S. region of residence), e-cigarette use (lifetime use, past 30-day use), lifetime cigarette use, interest in quitting e-cigarettes, use of vaping cessation services, and the presence of a serious mental health diagnosis, past month illicit drug use, or past year alcohol use disorder. For the presence of a serious mental health diagnosis and past month illicit drug use, potential participants will respond to a yes/no checklist of serious mental health disorders (e.g., bipolar disorder, schizophrenia) and illicit drugs (e.g., heroin, hallucinogens, cocaine). The Alcohol Use Disorders Identification Test-Consumption (AUDIT-C) will be used to screen for past year active alcohol use disorders with scores greater than four for men and three for women equating to the presence of an alcohol use disorder [32]. The basic demographics will be especially important for exploratory analyses of whether intervention effects differ based on these subgroups.

#### Baseline variables

The baseline survey will include an assessment of our primary and secondary outcomes (described further under Primary and Secondary Outcomes), which include e-cigarette use (e.g., past month use, days of use within the past 7 days), smoking susceptibility, perceptions of vaping- and smoking-related norms, and perceptions of vaping- and smoking-related harms. Further, we will assess for past year vaping quit attempts, motivation to quit vaping, quitting vaping self-efficacy, e-cigarette dependence, and the use of vaping harm reduction strategies. E-cigarette dependence will be measured with the E-cigarette Dependence Scale [33] and the use of vaping harm reduction strategies will be measured with the Vaping Protective Behavioral Strategies Scale [34].

#### Primary outcomes

Our primary outcomes are reductions in past 7-day self-reported vaping frequency (i.e., the number of days they vaped, the number of times per day they picked up their device to vape, and the number of puffs taken before putting their device away per day in the past 7 days), biochemically verified 7-day point prevalence abstinence, and smoking susceptibility using the 4-item Expanded Susceptibility to Smoking Index [35]. At each follow-up assessment, participants who report 7-day abstinence will be mailed a saliva cotinine test kit to provide biochemical verification of their abstinence. Participants will be provided with written instruction on how to perform the saliva cotinine test but will also be contacted by a research team member via a Zoom video call during verification to ensure that participants are able to correctly complete the test. Results will be provided immediately via the test strip and shown to the research team member to verify. Those with a cotinine level of < 30 ng/ml will be reported as having achieved biochemically verified nicotine vaping abstinence. Participants who complete this cotinine test will be compensated with a $20 Amazon gift card.

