### Exclusion criteria

Young adults who are currently receiving nicotine cessation services (e.g., counseling services, nicotine replacement therapies, quitline services, self-help materials, apps or other online supports for quitting vaping) will be excluded from the study. Those who report having been diagnosed with a serious mental illness (e.g., schizophrenia or schizoaffective disorder, bipolar disorder), having used an illicit drug in the past 30 days (e.g., cocaine, heroin), or screening positive for an alcohol use disorder in the past year will be ineligible, as they likely require a higher level of care.

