#### Covariates

Because the use of other tobacco products and substances are common in young adults [38–41], we will ask participants to report whether they have used other nicotine products (e.g., oral nicotine pouches, cigars, hookah), cannabis, and alcohol at baseline and follow-up timepoints. Those who indicate current use of other nicotine products (aside from combustible cigarettes) will not be excluded, as they may benefit from engaging in vaping cessation efforts. Additionally, because it is possible that participants may have initiated cigarette smoking during their participation in the study, we will also assess for cigarette use during our follow-up assessments.

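### The cotinine rule verifies abstinence from all nicotine, but the primary outcome is named vaping abstinence and users of other nicotine products are kept in

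*Protocol article*

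**What the plan says.** The Abstract and the Primary outcomes section make biochemically verified 7-day point prevalence abstinence a primary outcome, and the Abstract specifies that it concerns nicotine vaping.

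- **Who is tested, and when.** At each follow-up, "participants who report 7-day abstinence will be mailed a saliva cotinine test kit to provide biochemical verification of their abstinence". The participant is then "contacted by a research team member via a Zoom video call during verification", and the strip is read on that call. No maximum interval from survey to test is given.
- **The scoring rule.** Participants whose cotinine is below 30 ng/ml "will be reported as having achieved biochemically verified nicotine vaping abstinence". No other route to verified status is stated.
- **Other nicotine.** The Covariates section says: "Those who indicate current use of other nicotine products (aside from combustible cigarettes) will not be excluded". It describes use of other tobacco products and substances as common in this age group. Participants are asked "whether they have used other nicotine products (e.g., oral nicotine pouches, cigars, hookah), cannabis, and alcohol at baseline and follow-up timepoints". Because some may start smoking during the study, "we will also assess for cigarette use during our follow-up assessments".
- **Nicotine replacement.** The Exclusion criteria rule out "Young adults who are currently receiving nicotine cessation services (e.g., counseling services, nicotine replacement therapies" and similar supports. This applies to use at entry.
- **Analysis.** Abstinence is compared between arms by logistic regression, and those lost to follow-up count as treatment failures (Primary analysis). Neither this section nor Covariates links reported use of other nicotine or cigarettes to the scoring of abstinence.

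**The concern.** Cotinine is a marker of nicotine, not of the device that delivered it. The plan admits several other sources: products allowed at entry, cigarettes started during follow-up, and nicotine replacement begun after entry. A person who has truly stopped vaping can therefore test at or above 30 ng/ml.

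The Covariates section keeps users of other products in because they may gain from trying to quit vaping. The verification rule can deny those same people a verified success when they do quit.

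At stake is the only biochemically verified primary outcome. If the affected share is equal in both arms, the difference shrinks and power falls. If it differs by arm, the estimated effect is biased. A difference is possible because only the intervention arm receives quitting strategies before week 8, but the document gives no evidence of one in either direction.

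The survey and the test also refer to different days. The test follows the survey by the mailing and scheduling time, which is not stated.

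**Working it through.** **The plan's own figures.** The document gives no abstinence rate, no share of quitters using other nicotine and no mailing delay. Its only sample-size figures (62, 24 and 10 for f = 0.15, 0.25 and 0.45) are reproduced by a repeated-measures F test of the group-by-time interaction, assuming 4 time points and a correlation of 0.5. They do not concern abstinence and are not in dispute here.

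**Step 1: the rule as written.** Take a self-reported vaping abstainer who uses another nicotine product.

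- Cotinine below 30 ng/ml: verified.
- Cotinine at or above 30 ng/ml: not verified, whatever the source. The other-product answer is recorded as a covariate, and a covariate in a regression does not change a participant's outcome value.

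The verified set is therefore those free of nicotine from every source (to the test's cut-off), not those free of vaping.

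**Step 2: illustration of size.** Let u be the share of true vaping quitters who are at or above the cut-off because of other nicotine. Then

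observed rate = true rate × (1 − u).

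From the document: 50 per arm, alpha 0.05. Assumed: two-sided test, true rates of 15% (control) and 30% (intervention), and the values of u. Power is exact, for the pooled two-proportion z test. The odds ratio is shown because logistic regression is planned.

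| u control | u intervention | Observed control | Observed intervention | Difference (points) | Odds ratio | Power |
|---|---|---|---|---|---|---|
| 0 | 0 | 15% | 30% | 15 | (0.30/0.70)/(0.15/0.85) = 2.43 | 44% |
| 10% | 10% | 0.15 × 0.90 = 13.5% | 0.30 × 0.90 = 27% | 13.5 | (0.27/0.73)/(0.135/0.865) = 2.37 | 40% |
| 30% | 30% | 0.15 × 0.70 = 10.5% | 0.30 × 0.70 = 21% | 10.5 | (0.21/0.79)/(0.105/0.895) = 2.27 | 32% |
| 20% | 40% | 0.15 × 0.80 = 12% | 0.30 × 0.60 = 18% | 6 | (0.18/0.82)/(0.12/0.88) = 1.61 | 14% |
| 40% | 20% | 0.15 × 0.60 = 9% | 0.30 × 0.80 = 24% | 15 | (0.24/0.76)/(0.09/0.91) = 3.19 | 55% |

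With equal u, the ratio of rates stays at 2, the odds ratio moves little, and the loss is mainly of precision. With unequal u, the odds ratio moves below or above its true value, depending on which arm is more affected.

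**Step 3: timing.** If the test is taken d days after the survey, a test that looked back a full 7 days would share 7 − d days with the reported window: 5 days at d = 2, 2 days at d = 5, none at d = 7 or more. Both d and the look-back are assumptions. The error runs both ways: a truthful reporter who resumes vaping before the test fails, and a misreporter who stops before the kit arrives can pass.

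**The case against.** The strongest reply has four parts.

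1. **The plan does not say that such quitters are scored as failures.** It says who is verified, and it uses the word failure only for those lost to follow-up. A reader might infer a stated failure rule; there is none, and how a cotinine-positive abstainer is adjudicated could be set in the full protocol. This stands as a limit on wording. The mismatch remains, because the article does fix the success criterion and its label, and that criterion cannot be met by someone at or above the cut-off.
2. **Not every user of another product will exceed the cut-off.** A reader might infer that all of them stay above 30 ng/ml. The Covariates section names product types, not frequency, so this is unsupported. For that reason u is defined above as the share at or above the cut-off; read as the share of all users, it would give an upper bound on the loss.
3. **The plan foresees concurrent nicotine use.** It asks about it at every follow-up, and the vaping-frequency outcome already includes days vaped in the past 7, where zero is self-reported abstinence. This is true, and it makes the repair cheap. It does not alter the verified outcome. Vaping frequency and smoking susceptibility are unaffected by the specificity of cotinine.
4. **The bias has no known direction.** A reader might infer that the intervention effect is understated. No passage supports that: the last two rows of the table point in opposite directions, and so do the two timing errors. This stands in full.

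Some delay between survey and test is also unavoidable when only self-reported abstainers are tested remotely.

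**Conclusion.** The point holds as a mismatch between the name of a primary outcome and the test that defines it. Followed as written, the outcome is verified abstinence from all nicotine in a trial that deliberately includes users of other nicotine, and the information collected on that use is not connected to the scoring.

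The document does not allow the effect to be sized. On assumed true rates of 15% vs 30%, power goes from 44% to between 40% and 32% for shares of 10% to 30% equal in both arms; unequal shares give anything from 14% to 55% in the cases shown. These are illustrations, not estimates, and they do not show that the result will be biased or in which direction.

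The timing gap is a secondary point: it is real, of unknown size, and can act either way. The trial remains interpretable, but a claim about verified vaping abstinence would not rest on what was measured.

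**What to change.** 1. Name the cotinine outcome *verified abstinence from all nicotine*.
2. Pre-specify beside it a *vaping abstinence* outcome. Participants who report other nicotine or cigarette use at that follow-up are classified by self-reported vaping and flagged as not verifiable by cotinine; all others are classified by cotinine. Add a sensitivity analysis that counts the flagged participants as not abstinent.
3. At the video call already planned, re-ask past-7-day vaping and other nicotine use, and record the number of days from survey to test.

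**Cost.** Changed outcome wording, a few questions in an existing call and one extra analysis; no new visit, assay or participants.

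**Downsides.** Two abstinence definitions are reported. The self-report branch could count a continuing vaper who reports another product as abstinent; the sensitivity analysis bounds that error. The answers at the call describe days after the scheduled assessment, so they should sit beside the survey answer and not replace it. Recording the interval shows the timing gap but does not remove the notice a participant has before testing.
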